## Abstract

**Introduction:**

Managing mood, cognition and fatigue are top unmet needs reported by stroke survivors, which impact quality of life. There is currently no standardised UK care pathway to support post-stroke psychological outcomes. The ENhanced Reviews of PsychologIcal Changes (ENRICH) programme, an intervention co-designed with stroke survivors, carers and healthcare professionals, aims to fill this gap. Here, we describe the protocol for evaluating the feasibility and acceptability of ENRICH.

**Methods and analysis:**

ENRICH reviews comprise cognition, mood and fatigue assessment, personalised psychoeducation and tools to communicate results and discuss self-management strategies, delivered at 1, 3 and 6 months post-stroke. N=140 participants (N=80 patients who had a stroke, N=45 carers, N=15 healthcare professionals) will be recruited to a single-arm multicentre feasibility study.

Patients who had a stroke and carers will complete demographics at baseline (T1) questionnaires of quality of life, mood and healthcare resource use at 6 months post-stroke (T2) and an optional interview on experiences of ENRICH. Process evaluation will include fidelity assessment via audio recordings. Descriptive statistics will be calculated for study outcomes.

Key qualitative acceptability outcomes are sought on intervention delivery by clinicians, patients and carers.

Key intervention delivery feasibility outcomes relate to training clinicians (including competency and fidelity delivering ENRICH), and review completion rates. Study feasibility outcomes will include site and participant recruitment and retention rates and completion of candidate primary outcome measures on quality of life.

**Ethics and dissemination:**

The ENRICH study was approved by a UK Research Ethics Committee (reference: 24/LO/0341). Consent procedures include a waiver of consent to the intervention itself due ENRICH’s service-level design and written informed consent/consultee advice for participants providing research data. Results will be disseminated through peer-reviewed publications, conferences and lay summaries for study participants and healthcare professionals. Results will inform whether ENRICH is acceptable to delivering clinicians and receiving patients who had a stroke and carers, and provide key insights to inform a future randomised trial to determine effectiveness.

**Trial registration number:**

ISRCTN16018388.

STRENGTHS AND LIMITATIONS OF THIS STUDYMixed-methods design: This study uses both quantitative and qualitative data to comprehensively assess key uncertainties in the feasibility study to capture both depth and breadth.Fidelity monitoring: We will capture adherence to the ENhanced Reviews of PsychologIcal Changes (ENRICH) protocol in depth via self-reported fidelity checklists and audio recordings of intervention sessions.Patient and public involvement: We have thoroughly reviewed study materials and selected candidate primary outcome measures with input from those with lived experience of stroke and their family members.No control arm: Due to prioritising information about how the novel, co-produced intervention is delivered in sites, we have used a single-arm multicentre feasibility study design.No randomisation: Participants are not randomised to receive the ENRICH intervention.

## Introduction

 Stroke is a chronic neurological condition that is the number one cause of disability globally.^1^ The majority of stroke survivors experience psychological changes such as cognitive impairment, depression, anxiety and fatigue. Post-stroke cognitive impairment can affect domains of memory, attention, language, executive functioning and number processing abilities, with 6-month prevalence of any type of cognitive impairment as high as 68%.^2^ Post-stroke depression and anxiety are also common, affecting roughly 25–30% of stroke survivors.^3 4^ Finally, post-stroke fatigue rates reach up to 50% in terms of prevalence.^5^

Screening for post-stroke psychological changes, such as mood and cognition, is now recommended by national and international clinical guidelines for stroke.^6^ However, managing mood and cognitive changes are the top two unmet needs following stroke, alongside other psychological outcomes.^7^ Further, 81.4% of stroke survivors and carers report wanting more information on managing and understanding psychological changes after stroke^8^ with clearly evidenced psychoeducation needs on post-stroke cognition.^9^ Despite improvements in the first 6 months post-stroke,^10^ psychological changes can persist chronically, with prevalence rates long-term post stroke ranging from 25% to 50%.^11^

Providing ongoing support for psychological changes is especially important because these changes have a substantial impact on post-stroke quality of life.^2 11^ Importantly, research on the topics of post-stroke mood and cognitive changes was ranked as the top two priorities within the most recent James Lind Alliance priority setting exercise.^7^ In the UK, the National Health Service (NHS) recommends that all patients who had a stroke are offered a single 6-month review of their recovery and abilities following discharge from acute/subacute stroke services. However, the current stroke care pathway does not routinely provide care for recognising, understanding and managing post-stroke psychological outcomes, with many reviews primarily focused on secondary stroke prevention or on physical stroke recovery (eg, blood pressure monitoring, medication review^12^). This is in part due to a lack of sufficient training on how to screen for and communicate post-stroke psychological outcomes and inconsistency in post-stroke reviews provided across the UK.

The ENhanced Reviews of PsychologIcal Changes (ENRICH) intervention was developed iteratively and rigorously following the Medical Research Council (MRC) framework for complex intervention development,^13^ detailed in Hobden and Demeyere.^14^ The final ENRICH intervention consists of an iterative (1, 3 and 6 months) monitoring and management programme for post-stroke psychological changes using ENRICH reviews. Each ENRICH review provides assessment, feedback and personalised psychoeducation on domain-specific cognition, mood and fatigue, with self-management strategies and onward referral to specialist services as indicated. The ENRICH training and reviews also emphasise non-specific elements of psychological care, such as personalisation, explaining jargon, fostering hope and optimism and using compassion and sensitivity throughout the reviews. The ENRICH intervention provides a holistic framework for enhancing the psychological care pathway for stroke survivors.

In this study, we aim to determine the feasibility, acceptability and fidelity of ENRICH reviews delivered in clinical stroke services by a range of healthcare professionals to inform a potential future pragmatic randomised cluster trial.

## Methods and analysis

### Design

The ENRICH feasibility study is a single arm multicentre feasibility study across two sites, delivered at the site/cluster level, capturing detailed quantitative and qualitative data on feasibility, acceptability and fidelity focused primarily on the ENRICH intervention itself, aimed at informing the design of a future pragmatic cluster randomised controlled trial. We considered a site to be at least one NHS stroke service comprising the full stroke care pathway from acute to 6 months post-stroke. Where this comprised two separate services, this was considered one site for the purposes of delivering the ENRICH intervention.

#### Our specific aims were to evaluate

Acceptability of ENRICH to NHS healthcare professionals, patients who had a stroke and family members, and of quality of life and health economic outcome measures.Feasibility of site recruitment, participant recruitment and retention rates, most effective methods of consent and delivery of ENRICH reviews.Fidelity of the ENRICH intervention when delivered by NHS healthcare professionals.

All recruited sites will only be required to implement the ENRICH intervention (ie, no control site). Given data in acute and subacute stroke populations on recruiting and conducting complex interventions at the cluster level using controlled designs,^15^,^17^ we have adopted a design to capture the most relevant data and prioritise evaluation of ENRICH intervention training and delivery, to inform progression to a pragmatic effectiveness trial. We include a waiver of consent for the ENRICH intervention delivery only in accordance with the Ottawa statement on Ethical Design and Conduct of Cluster Randomised Trials,^18^ given that the intervention is arguably in line with minimum stroke care standards and is unlikely to cause harm. The waiver of consent covers the delivery of the full ENRICH intervention delivered at 1, 3 and 6 months post-stroke, including conducting the assessments, communicating screening results and self-management of psychological changes (see ENRICH intervention below for further specifics). A single-arm multicentre feasibility study design with a waiver of consent for intervention delivery was selected because (1) ENRICH was designed to be implemented for all patients who had a stroke in a service as a standard of psychological care; (2) we aim to evaluate the ENRICH intervention as a service change for all, rather than an intervention for only a specific subset of patients who had a stroke, and (3) there was deemed a potential for contamination within a service where ENRICH-trained healthcare professionals typically jointly discuss patients who had a stroke care, thereby also limiting the potential for evaluation within an individually randomised controlled trial.

The waiver of consent does not cover transfer of any research data about the ENRICH assessments or identifiable patient demographics to the research team outside of the patient’s NHS service. Written informed consent or favourable consultee advice is required to be in place for this research data collection to occur. Only fully anonymised site-level information will be collected about total number of patients in the recruited site who had received an ENRICH review during the study time frame. Patients lacking capacity will be protected through having consultee advice procedures in place, conducting with a family member who knows the patient well, to advise on what they believe the patient would have wanted with regards to research data collection.

We set out to evaluate context-specific uncertainties prior to an effectiveness trial to maximise usefulness of information gained, in line with the MRC complex intervention framework for feasibility studies.^13^ The ENRICH intervention was envisioned as a service change, with the ultimate implementation aim to deliver enhanced reviews to all patients who had a stroke as a new Level 2 standard^19^ of post-stroke psychological care in line with clinical recommendations.^20^ Here, we closely aligned the intervention development with consensus views on what psychological care should look like^21^ and aimed to evaluate this complex intervention through a future implementation lens in line with integrating implementation goals closely within the complex intervention evaluation.

The ENRICH key uncertainties, as identified with stakeholder involvement, related mainly to study design, intervention delivery and research data collection elements.

#### Uncertainties in Study Design

Given the focus on intervention delivery in the first 6 months post-stroke where active care is still present, it was unknown how many sites would be eligible (see Participants section for inclusion/exclusion criteria) and interested in taking part in ENRICH. Further, it was unknown if during this point of active care delivery whether sufficient patients who had a stroke and family members numbers could be recruited to research data collection, and whether the recruited stroke sample was comparable to non-consenting clinical populations (eg, in terms of stroke severity, degree of cognitive impairment).

Uncertainty exists on whether a future randomised cluster design, with a waiver of consent to the intervention itself, would be feasible in terms of number of reviews delivered to non-consenting patients who had a stroke, and to what degree each consenting method (standard consent, consultee advice) would be used throughout the trial. Finally, given the wide variation in how psychological stroke care is provided across services, it is unknown what the minimum care standard for a future potential control arm would look like.

### Uncertainties in Intervention Delivery

Given that ENRICH is a novel, co-produced intervention, the acceptability of the reviews by patients who had a stroke, family members and healthcare professionals is unknown. Second, as ENRICH was designed to be delivered over an extended time frame post-stroke by members of the stroke care team, the feasibility of training a variety of clinicians to deliver the ENRICH reviews with high adherence to the key intervention requirements was identified as another key uncertainty.

### Uncertainties in Research Data Collection

It was unknown what the estimated completion rates and attrition would be for completion of the outcome measures, as well as uncertainty around which of two candidate quality of life outcome measures to use and whether health economic data could be captured adequately (see Outcomes for details on study measures). Further, it was unknown whether participants would find collecting fidelity data (see Fidelity section below) acceptable.

Taken together, we aimed to investigate acceptability and feasibility of the intervention delivery, as well as design feasibility of a future cluster design including waiver of consent for delivery of the ENRICH intervention. A summary of our key uncertainties and associated data we aim to collect is in table 1. Our qualitative aims with regards to delivering the intervention were to explore the acceptability of the ENRICH training by healthcare professionals and the ENRICH reviews by patients who had a stroke, carers and healthcare professionals through surveys and interviews. In addition, we will examine the fidelity to non-specific factors through audio recordings of reviews and explore barriers and facilitators of the implementation of the ENRICH reviews in clinical stroke services. With regards to study design, we aim to explore participants’ views on study procedures, materials and outcome measures, alongside understanding standard clinical care.

**Table 1 T1:** Summary of key uncertainties and associated data to be collected

Evaluation domain	Study component	Data source	Key uncertainty	Associated quantitative data	Associated qualitative data
**Feasibility**	**Study design**	Sites	Can we recruit sites?	Number of eligible sites expressing interest	
			How many patients receive ENRICH with waiver of consent?	Total number of reviews delivered	
			What is the standard of care?	Number of non-ENRICH clinical contacts	Descriptions of standard care across each recruited site
		Healthcare professionals	What is the most effective consent method?	Proportion consented by clinician role	
			Can we recruit and retain sufficient numbers?	Recruitment and attrition rates	
		Patients who had a stroke	Can we recruit and retain sufficient numbers?	Recruitment and attrition rates	
			Can we recruit a diverse sample?	Patient demographics vs national audit data	
			How many ENRICH reviews do participants receive?	ENRICH review completion rates	Reasons for non-completion
		Family members	Can we recruit and retain sufficient numbers?	Recruitment and attrition rates	
Acceptability	Intervention delivery	Healthcare professionals	Can we train a variety of healthcare professionals to deliver ENRICH?	Numbers trained per site	Training survey feedback and interviews
			What are their views on ENRICH?	Helpfulness and usefulness ratings of ENRICH	Interviews on barriers and facilitators to ENRICH
			How many of those trained deliver the intervention?	Proportion of those trained delivering ENRICH	
		Patients who had a stroke	What are their views on ENRICH?	Helpfulness and usefulness ratings of ENRICH	Interviews on acceptability of ENRICH
		Family members	What are their views on ENRICH?	Helpfulness and usefulness ratings of ENRICH	Interviews on acceptability of ENRICH
	Research data collection	Patients who had a stroke and Site principal investigators	Which candidate primary outcome measure is best to use?	QOLIBRI and WHO-QOL-BREF completion rates	Interviews on acceptability of QOLIBRI and WHO-QOL-BREF
			Can we collect health economic information?	HEQ completion rates	
			Can we collect process outcome measures?	Process measure completion rates	
			Can we collect audio recorded fidelity data?	Proportion consenting to audio recordings	
Fidelity	Intervention delivery	Healthcare professionals	Are ENRICH intervention components delivered with high fidelity?	Completion checklists of intervention components; ratings of intervention audio recordings	

ENRICH, ENhanced Reviews of PsychologIcal Changes; HEQ, Health Economics Questionnaire; QOLIBRI, Quality of Life Instrument after Brain Injury; WHO-QOL-BREF, WHO-Quality of Life-Brief.

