### Key Secondary Outcome Measures—Candidate Primary Outcome Measures for a Future Trial

In order to ultimately evaluate whether ENRICH is an effective intervention, a future effectiveness trial should evaluate a meaningful outcome. In collaboration with our PCPI group, the candidate primary outcome for future evaluation was determined to be quality of life. In the present study, these are key secondary outcome measures relative to the primary outcome measures assessing feasibility above. Following PCPI discussions, we selected two potential candidate primary outcome measures as below, for which we aimed to determine acceptability and completion rates in the present study.

The Quality of Life Instrument after Brain Injury (QOLIBRI) is a 37-item self-report measure of health-related quality of life following brain injury. The measure is designed to measure aspects of health-related quality of life associated specifically with brain injury such as thinking abilities, emotions, functioning and social activities and the degree to which individuals are bothered by them. The QOLIBRI was specifically developed and validated for brain injury populations.^27^

The WHO-Quality of Life-Brief (WHO-QOL-BREF) is a 39-item patient-reported outcome measure designed to capture quality of life across physical, psychological and environmental domains and capture how quality of life has been affected by disability. The WHO-QOL-BREF has been validated for patient use across multiple patient populations including stroke.^28^

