### Quantitative Data for Uncertainties in Research Data Collection

We aim to assess completion rates of candidate outcome measures (ie, total proportion of participants completing each outcome measure) at T2 to inform acceptability. We will additionally assess total proportion of patients consenting to audio recordings for fidelity. Through the HEQ, we will additionally assess number of healthcare services used to describe usual care and inform the future control arm.

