### Qualitative Data for Uncertainties in Research Data Collection

In interviews, we will explore the acceptability of the candidate primary outcome measures (QOLIBRI and WHO-QOL-BREF) and the health economic measure (HEQ) given limited use of these measures in stroke. We will also explore acceptability of reviews being recorded for fidelity purposes.

From recruited sites, we will collect surveys on descriptions of usual care to inform what a future control arm would look like.

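### The data assigned to choosing between QOLIBRI and WHO-QOL-BREF are completion and acceptability; the score distributions, already collected, are not linked to the choice

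*Protocol article*

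**What the plan says.** In the protocol article, Table 1 (research data collection rows) poses the question "Which candidate primary outcome measure is best to use" and sets two kinds of data against it: "QOLIBRI and WHO-QOL-BREF completion rates" on the quantitative side and "Interviews on acceptability of QOLIBRI and WHO-QOL-BREF" on the qualitative side.

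Other sections agree:

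- The section on key secondary outcome measures introduces the two instruments as candidates "for which we aimed to determine acceptability and completion rates in the present study".
- The section on quantitative data for research data collection defines completion as the "total proportion of participants completing each outcome measure) at T2 to inform acceptability".
- The matching qualitative section explores acceptability in interviews, "given limited use of these measures in stroke".

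On background validation, the key secondary outcomes section states that "The QOLIBRI was specifically developed and validated for brain injury populations", without naming stroke. It says that WHO-QOL-BREF has been validated in several patient populations, stroke among them.

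Table 3 shows both instruments at T2 only. The Quantitative Analysis section will summarise the T2 outcome measures descriptively, as a general summary with no reference to the choice of instrument.

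**The concern.** The question is which instrument should carry the primary outcome of an effectiveness trial. Completion shows whether patients will fill in the form. Interviews add burden and, probably, whether the content seems relevant. Neither shows whether the scores spread over the patients the trial will enrol or bunch at one end of the scale.

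The point is open on the article's own account: it refers to limited use of these measures in stroke, and it describes the eligibility criteria as intentionally broad. An instrument that is easy to complete but compressed at its floor or ceiling could be preferred to one that discriminates better. The cost would fall on the later cluster trial as a smaller standardised effect and a larger sample. The data needed to look for this are already in the study.

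**Working it through.** **1. Inputs assigned to the choice.** Set side by side, Table 1, the key secondary outcomes section and the two sections on research data collection name the same two inputs, completion and acceptability. The one related progression criterion in Table 4 is also completion (green at 75% or more). No section names score range, spread or item-level missingness as an input.

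**2. Number of completers.** The Sample Size section gives up to 80 stroke participants, allowing for 25% attrition, with no formal calculation. 80 × (1 − 0.25) = 60, and 60 / 0.75 = 80. The 60 is derived here; the article does not state it.

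**3. Can completion separate the instruments?** At 60/80 = 75%, the exact 95% interval is 64% to 84%. The same patients receive both forms, so the comparison is paired and only patients who complete one form but not the other contribute. If all d such patients favour the same instrument, the exact McNemar p-value is 2 × 0.5^d:

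- d = 5: 2 × 0.5^5 = 0.063
- d = 6: 2 × 0.5^6 = 0.031

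So at least 6 of 80 (7.5 percentage points), all in one direction, are needed for p < 0.05. With an assumed 5% to 15% of discordant patients and no true difference, the 95% half-width is 1.96 × √(share/80), which is 4.9 points at 5% and 8.5 points at 15%. With stated lengths of 37 and 39 items at one assessment, near-equal completion is a plausible result and would settle little.

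**4. What a ceiling would cost.** Assumptions: latent quality of life is N(0,1) in controls and N(0.30,1) under treatment, and the observed score is min(latent, c), with c set so that a share f of controls is at the ceiling. The attenuated effect d* is the difference in capped means divided by the root mean of the two capped variances. The sample-size ratio is (0.30/d*)².

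| Share at ceiling | d* | More patients |
|---|---|---|
| 5% | 0.297 | 2% |
| 10% | 0.294 | 4% |
| 15% | 0.289 | 7.5% |
| 20% | 0.285 | 11% |
| 30% | 0.274 | 20% |
| 40% | 0.262 | 31% |

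For example, at 20% the capped means differ by 0.226 and the pooled SD is 0.795. Then d* = 0.226/0.795 = 0.285, and (0.30/0.285)² is about 1.11.

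**5. Could about 60 completers show it?** Exact 95% intervals for the share at an extreme:

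- 3/60 = 5%: 1% to 14%
- 9/60 = 15%: 7% to 27%
- 15/60 = 25%: 15% to 38%

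Take, for illustration only, a flag raised when more than 15% (10 or more of 60) are at an extreme. It is raised with probability 0.1% if the true share is 5%, 41% if 15%, 95% if 25% and 99% if 30%. The 95% interval for the SD runs from 0.85 to 1.22 times the observed value. A gross problem would be seen; a moderate one might not be.

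**The case against.** The case on the other side has several parts.

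- **No decision rule is stated.** Table 1 is a summary of uncertainties and associated data. A reader might infer that the choice will be made from completion and interviews alone; the article never says so. This stands. The supportable statement is that these are the only data the article assigns to the question.
- **Psychometric summaries are analysis-plan detail.** The full protocol and analysis plan are not shown and may add criteria. This stands as a caution. It does not remove the point, because the article states the question and its inputs in several sections, and the inputs are the same each time.
- **The scores will be summarised anyway, and the advisory committee has trial statistician expertise.** True, and gross bunching might be noticed. This lowers the cost of the fix; it does not link the summaries to the choice.
- **Interviews can cover relevance of content, and the patient, carer and public committee selected both candidates.** This stands: it would be wrong to say that the inputs measure only willingness to fill in a form. Neither source shows the range of scores.
- **Suitability in stroke is not wholly unknown.** The article states that WHO-QOL-BREF has been validated in populations including stroke. A reader might also take the sample to be unrestricted in severity. The article says only that the criteria are broad, and Table 2 requires the ability to concentrate for 10 minutes and sufficient English.
- **A large ceiling is hypothetical.** On a total score, 20% to 40% at the maximum means that share giving the best answer to essentially every item. At 15% or less the cost is 7.5% or less. This stands, and is why the whole range is shown.
- **One arm with T2 scores only cannot show responsiveness.** This stands. The check concerns range and spread, and cannot by itself establish which measure is best.

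**Conclusion.** The point holds as an optional improvement. The article asks which measure is best, assigns completion rates and acceptability interviews to that question, and leaves the T2 score distributions, which it collects and summarises, unconnected to it.

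Under the normal-latent, 0.30 SD, capped-score model, the cost to the future trial runs from about 2% more patients at a 5% ceiling share to about 31% at 40%. The documents give no evidence on where either instrument falls in that range, so the figures show what is at stake and do not predict a problem. The stronger conclusion, that an unsuitable instrument will be chosen, is not supported. The feasibility study itself is not invalidated.

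**What to change.** In Table 1, and in the section on quantitative data for uncertainties in research data collection, add the following as inputs to the choice. Report them for each instrument, among participants with both instruments scored, with 95% intervals:

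- the share at the minimum and at the maximum, for total and domain scores;
- the SD;
- item-level missingness, which for a fair reading should also be reported among all who returned either form.

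State in advance the floor or ceiling share above which an instrument is not preferred on completion alone. The 15% used in the working is an illustration; the sponsor should choose and justify its own figure.

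Cost: a few descriptive lines from data already collected, with no new patients, visits or questionnaires. Downside: at about 60 completers the estimates are imprecise (an observed 15% has an interval of 7% to 27%), so the threshold should be read with its interval. Responsiveness to change would remain untested.
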